##### PHC users—interviews of the process evaluation (n=12–18 interviewees/arm): process evaluation

For the interviews, we will include PHC users with and without chronic conditions at pre-intervention, during intervention and post-intervention. These participants do not need to be the same each time. We will consider diversity of age groups to see how perception is affected by this characteristic.

##### Healthcare workers (n=6–10 healthcare workers/arm): qualitative and process evaluation

The number of healthcare workers to interview would depend on the workforce of each PHC centre. Ideally, six healthcare workers per arm across the three arms will be interviewed, for a total of 18–22 expected interviews per country.

However, during the implementation of the capacity building component, all the healthcare workers who participated will be included in the measurement of the indicators.

### Data collection procedures

#### Quantitative evaluation

Pre-intervention, an initial survey will be conducted to estimate the prevalence of chronic conditions of interest and to validate the tools used to define the primary outcomes (online supplemental tables 2, 3). Due to the context with low awareness of HTP and type 2 diabetes, this survey will identify adults with these conditions, invite them to the study, obtain informed consent and track them every 3 months. Information will be collected using appropriate technology strategies such as REDCap templates with trained fieldworkers. The survey instrument is detailed in online supplemental material 4.

Questionnaires of the initial survey will contain primary outcomes (eg, PSQ-18, health responsiveness) as well as other indicators of interest (eg, People’s Voice Survey). Overall information will be collected as part of the initial survey, but also in five different moments during the project. As tools used to inform primary outcomes were developed in English, data collected from the initial survey will be used to validate and adapt such tools. The characteristics and timing of the outcomes are detailed in table 3. Thus, we estimate that for this survey, we will need a minimum of 420 participants per country (70 per PHC centre), stratified by sex (ie, 210 males and 210 females). In addition, some anthropometric markers such as height and weight will be measured using a stadiometer and validated scales, respectively. Blood pressure will also be measured using automated devices (OMRON HEM-780), validated for population-based studies, and using standardised procedures.^42^ Blood pressure will be evaluated after 5 min of resting and in the right arm. Measurements will be done in triplicate, with a separation of at least 1 min between measures, and the average of the second and third assessment will be used to determine blood pressure level, HTP and control.

Information from the initial survey will be used to decide the inclusion of relevant questions and topics used to assess the intervention. Primary and secondary outcomes will be evaluated at different moments (see details in table 3). Multiple assessments will be done in specific subpopulations (ie, those having a diagnosis of HTP, those having a diagnosis of type 2 diabetes or users of PHC centres). To evaluate HTP control, we plan to measure blood pressure levels according to the aforementioned techniques. For those with diabetes, random glucose sampling using a validated glucometer as well as the time of the last meal (ie, number of hours lapsed from last meal) will be considered to identify those under appropriate control as in a previous study in resource-constrained settings.^43^

Regarding the communication strategy, it will be integrated within the quantitative evaluations and process evaluation. The knowledge and habit questionnaires will contain the related outcomes (ie, understanding of the concept, risks and symptoms, prevention and control, and behaviour, intention and attitude). Outcomes of the communication strategy will be evaluated at pre and post (table 3). Assessments will also be conducted in specific populations (ie, those having HTP, diabetes and users of PHC centres).

#### Qualitative evaluation

##### Qualitative longitudinal study with health service users

Data will be collected through in-depth interviews and, when possible, if participants accept photo-elicitation, it will be used to evoke conversations during the interviews. Each interview will be conducted by two interviewers and could last 1–1.5 hours. The interview guide will explore how participants’ individual expectations and experiences using the local health services change *through time* as a result of the intervention and how this is reflected in their use, perceived value and satisfaction of the health services. Each participant will be interviewed three times. Additionally, at the end of the first and second interviews, participants will be offered the possibility of taking pictures using a disposable camera provided by the project. These pictures should illustrate what it means for participants to live with a chronic condition, including their experience using the health services. When applicable, the pictures will be used to initiate conversations in the second and third interviews. Because this would be the first time that photo-elicitation is used in the study settings, the potential response by participants is unknown. Depending on the participant’s acceptance to photo-elicitation in the first data collection moment, the research team will assess whether to continue or suspend the activity for the second moment. If participants agree, a local photo exhibition will be organised after the implementation of the interventions and all the evaluations are concluded to display a selection of the pictures. The research team will register their experiences in an individual reflexive diary, and structured summaries of debriefing meetings will be prepared for each data collection moment.

##### Qualitative study with healthcare workers

Data will be collected through interviews at three points. The qualitative study will examine the perception of healthcare workers of their roles, responsibilities and capacity to deliver services. The qualitative research team will conduct the interviews and will use the interview transcripts for data analysis.

### Economic evaluation

Data will be collected at different points in time. Facility-level data will be collected at the initial survey and at moment 5. Data on household out-of-pocket payments will be collected in parallel with the quantitative evaluation. For the ‘care as usual’ arm, guidelines and protocols for the first level of care for diabetes, HTP and NTDs will be sought to identify the procedures and supplies to provide care at each country, complemented with interviews with key informants. For the intervention arm, we will meet with the research team who participated in co-creation and co-design processes to identify activities and information details for each country. The COHESION co-creation manual will be used to list the expected activities.^44^ An interview guide with a pre-filled checklist of activities will be applied, and administrative records will be reviewed to reduce recall bias and capture resource use to implement the intervention. It is important to mention that the COVID-19 pandemic and funding issues caused a 4-year delay between co-creation and co-design, impacting costs. For that reason, we will compare real and hypothetical costs where co-design followed immediately after co-creation. Interviews to account for the resources used will be made. Healthcare workers in each PHC centre will record all inputs used in a logbook, and this information will pre-fill cost data collection forms. In addition to the healthcare perspective, we will apply a survey to capture out-of-pocket payments from households and other household costs to be included in the societal perspective.

#### Cost calculation

Cost calculation will follow a bottom-up strategy using pre-filled data collection forms to gather information on resources used, frequencies, prices and costs. Data will be collected through interviews with key informants, on-site observation and document review. Household cost assessment will involve interviews with community members to document travel time, medicines expenses, laboratory test, consultations and other inputs. We will ask if another family or community member had to accompany them and absenteeism from work.

A form will be prepared to collect data on health resources at the facility level such as services provided, number of monthly users, infrastructure utilisation, equipment and number of human resources. An employee list will identify relevant healthcare workers for the health services under study, along with a list of expected supplies and medicines according to national guidelines. We will adapt data collection forms from the WHO Mother Baby Package Costing Tool. To collect data on resources at the household level, we will interview individuals with one or more health conditions identified in the quantitative evaluation, both users and non-users of PHC services, to capture household characteristics and healthcare expenditures, including transportation costs and lost wages. Instruments will be developed using the Living Standards Measurement Study guidelines.

Costs will be classified by input, specifically into capital and recurrent cost categories. Capital costs include large equipment, buildings, one-time training for healthcare workers and social mobilisation. Recurrent costs include supplies such as drugs, syringes, consumables and small equipment; periodic training costs such as short courses; personnel costs; operation and maintenance of buildings and vehicles; and social mobilisation costs.

### Process evaluation

Quantitative data will be collected through surveys and checklists, and qualitative data through semi-structured interviews. The data on the health system indicators will be collected in both intervention and usual care arms.

For PHC users, a guide will be implemented to document (1) services users’ perceptions of the intervention by healthcare workers; (2) perceptions about changes in the treatment received at PHC; (3) perceptions about the communication through different communications channels (eg, community-based loudspeakers, radio, community word of mouth) and (4) reach of the communication strategy and their impact. Non-intervention community members will be interviewed similarly, with questions adapted to reflect their exposure to health-related radio programmes or podcasts and the messages they recall. For non-PHC service users, information will be collected to understand why they are not using the health services from the PHC. For healthcare workers, a guide will be conducted to explore (1) why healthcare workers did use or not use the training received during the intervention, (2) how the co-designed intervention was implemented in their everyday practice and (3) what is the impact of the intervention in terms of communication between healthcare workers and service users. Some questions of the qualitative evaluation study will be integrated as mentioned previously. Finally, for decision-makers, relevant public health stakeholders (regional health directorate) will be interviewed to explore the possibilities to uptake the intervention and scaling up.

As part of the communication strategy, qualitative data will be gathered through in-depth interviews conducted within the process evaluation. Information will be collected to document the comprehension of chronic diseases, the exposition and remembrance of themes and messages of spots, interview programmes or podcast. Outcomes will be evaluated once during the project intervention (table 3). Assessments will be performed within users diagnosed with HTP and diabetes.

### Analysis

#### Primary endpoint analysis

STATA 16.0 for Windows (StataCorp, College Station, Texas) will be used for statistical analysis. We will describe variables of interest, especially numerical outcomes such as patient satisfaction or health system responsiveness, using appropriate central tendency (mean, median, etc) and dispersion measures (SD, IQR, among others). An intent-to-treat analysis as well as a per-protocol analysis plan will be developed before starting statistical analysis. Given the nature of the intervention, a pre–post study with repeated measures, appropriate longitudinal and panel data analysis techniques will be used for the assessment of the outcomes. An analysis at the individual level using generalised estimating equations or linear mixed models would be preferable to flexible handling of normal or non-normal variables. These models tend to be more robust to misspecification of the variance structure since ‘sandwich’ type variance estimates are used.^45 46^ A string of consecutive observations equally spaced in time is planned to have multiple assessments pre-intervention and post-intervention. In this way, we will be able to account for two of the most common issues in this type of quasi-experimental studies: confounding and regression to the mean.^47^ Due to the lack of randomisation in our sample, other potential confounders at the individual, but also at the setting level, will be also considered.

#### Secondary endpoint analysis

Similar to the aforementioned analysis, secondary endpoint outcomes will be assessed graphically and using tabulations (eg, access to HTP care, access to diabetes care). The effect of the intervention on our outcomes will be conducted using generalised estimating equations or mixed models (linear or logistic depending on the type of variable). Potential confounders will also be considered. As usual, other analyses will be conducted to explain the effect of the intervention, if any, on main and secondary outcomes. This includes, but is not limited to, stratification by sex, analysis per specific chronic condition (eg, HTP, diabetes, country-specific NTD), etc.

#### Qualitative analysis

This study is grounded within interpretative approaches, in which interview data are seen to provide access to accounts of how respondents perceive, understand and talk about the world.^48 49^ The interviews will be recorded and transcribed verbatim in the local languages. The resulting transcripts will be analysed following the same procedure in the three countries, deductively (ie, coding data according to key elements of existing conceptual frameworks) and inductively (ie, using thematic analysis to elicit new themes or unexpected findings through coding and categorising of data) using the qualitative ATLAS.ti software. The data analysis will be done by a team speaking the local language, so no translation of the transcripts will be needed. However, to enable cross-country comparisons and the production of research outputs, synthesis tables will be completed in English by the local research teams to inform these comparison processes. Overall, intersectional-gender and sociocultural dimensions will be considered when analysing the data.

#### Economic analysis

A detailed micro-costing of the resources will be implemented, and descriptive statistics of the implementation resources and costs of the different strategies and usual care will be presented. Implementation and healthcare costs will be included in the cost-effectiveness analysis from the healthcare perspective. In addition to these costs, other direct and indirect costs will be included in the analysis from a societal perspective. The primary outcome of the economic evaluation will be the incremental cost-effectiveness ratio.

A sensitivity analysis will be performed by varying parameters such as the discount rate, among others, to account for uncertainty.

For cost-effectiveness analysis, primary outcomes indicators will be used (table 3). Assessment will consider patient satisfaction (PSQ-18) and health system responsiveness as primary outcomes. Each country team will set cut-off points to identify community satisfaction with services. Incremental cost-effectiveness ratios will be calculated as the difference in costs and effectiveness between intervention and usual care arms using both alternatives. For cost–utility analysis, we will evaluate two alternatives using EQ-5D-5L as outcome for quality-of-life measurement. Utility values will be derived by combining EQ-5D-5L results with pre-existing set of values (‘tariffs’). EQ-5D-5L and corresponding country value sets are validated in Nepal and Peru; Mozambique will use the international standard value set. Quality-adjusted life-years (QALYs) will be calculated by multiplying utility value for each alternative during 10-year incremental cost–utility ratios, which will be calculated using costs and QALY differential.

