**Methods and analysis:**

A mixed-methods, pre–post quasi-experimental design will be used, including quantitative, qualitative, economic and process evaluations. Each country will have three arms: (1) co-created and co-designed interventions; (2) only co-designed intervention and (3) the usual care arm. Data will be collected longitudinally over 18 months to assess the effect of the interventions. The main outcomes include patient satisfaction (Patient Satisfaction Questionnaire Short Form), health system responsiveness (WHO responsiveness domains) and quality of life (EuroQol 5 dimensions 5 levels). The qualitative evaluation will explore how satisfaction is perceived among service users with chronic conditions and healthcare workers. Other outcomes per type of evaluation will be considered such as perceived value of health services, cost estimation and acceptability of the intervention components, among others.

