#### Economic evaluation

An economic evaluation will be conducted, comparing two arms: care-as-usual (control) and the implementation of the co-design interventions. The evaluation will be conducted in three distinct phases: (1) implementation only, (2) co-design and implementation, and (3) co-creation, co-design and implementation. A cost-effectiveness and cost–utility analysis will be conducted. The study will adopt a dual perspective, examining both the healthcare sector (ie, the Ministry of Health of each country) and the societal (ie, households) perspectives. The time horizon over which costs and consequences will be evaluated is 3 years, and the discount rate will be 10% according to national rates. The relatively short time horizon and the discount rate will be considered as parameters in a sensitivity analysis.

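### The economic plan sets a 3-year horizon for costs and consequences, yet attaches 10 years to the QALY or cost-utility calculation; the two statements must be reconciled.

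*Protocol article*

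**What the plan says.** Protocol article, Study design, Economic evaluation: "The time horizon over which costs and consequences will be evaluated is 3 years". The same paragraph adds that "the discount rate will be 10% according to national rates", with no separate rate for QALYs, and that "The relatively short time horizon and the discount rate will be considered as parameters in a sensitivity analysis". It names no alternative horizon.

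Protocol article, Analysis, Economic analysis: "Utility values will be derived by combining EQ-5D-5L results with pre-existing set of values". QALYs are then "calculated by multiplying utility value for each alternative during 10-year". The sentence continues without a break into the incremental cost-utility ratios, "which will be calculated using costs and QALY differential". Nothing there marks the 10 years as a sensitivity or extrapolation analysis. The section's separate sentence on sensitivity analysis names only the discount rate as an example.

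On the data available, the Abstract states: "Data will be collected longitudinally over 18 months to assess the effect of the interventions". The Intervention section gives a duration of 7 months. Table 3 lists cost per QALY gained among the primary economic outcomes and schedules EQ-5D-5L at the initial survey and at Moments 2 to 5.

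**The concern.** Two analysts, one working from the Study design section and one from the Analysis section, would report different values of a primary economic outcome from the same data. The worst combination takes costs over 3 years and QALYs over 10. The numerator and denominator of the ratio then cover different periods, and cost per QALY looks cheaper than the declared horizon supports. Whether or not costs are also taken over 10 years, a utility difference observed for at most 18 months would be carried forward for years without a stated basis.

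There is a smaller, related risk. The formula multiplies each alternative's utility level, not its change, and the arms are not randomised. Unless baseline utility is adjusted for, a difference that existed before the intervention would count as a gain.

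**Working it through.** The article gives no utility gain, QALY total or cost-utility ratio, so there is no figure of its own to reproduce. What can be checked is how far the two periods differ.

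**Inputs from the Protocol article**
- Horizon for costs and consequences: 3 years (Study design, Economic evaluation).
- Period attached to the QALY or cost-utility calculation: 10 years (Economic analysis).
- Discount rate: 10% per year (Study design, Economic evaluation).

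**Assumption.** The annual utility difference is constant over the period, as multiplying a utility value by time implies.

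**Discount factor.** A(T, r) = (1 − (1 + r)^−T) / r
- A(3, 0.10) = (1 − 1.1^−3) / 0.10 = 2.487
- A(10, 0.10) = (1 − 1.1^−10) / 0.10 = 6.145
- Ratio = 6.145 / 2.487 = 2.47
- Fall in cost per QALY if costs stay at 3 years: 1 − 1/2.47 = 0.595, about 60%

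Counting each year's QALYs at the start or at the end of the year gives the same ratio.

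**Other discount rates, constant difference**

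| Rate | 3 years | 10 years | Ratio |
|---|---|---|---|
| 0% | 3.000 | 10.000 | 3.33 |
| 3% | 2.829 | 8.530 | 3.02 |
| 5% | 2.723 | 7.722 | 2.84 |
| 10% | 2.487 | 6.145 | 2.47 |
| 12% | 2.402 | 5.650 | 2.35 |

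**Waning gain at 10%** (assumed patterns, summed by month, so the 3-year factor for a constant gain is 2.609 instead of 2.487)

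| Pattern of the gain | 3 years | 10 years | Ratio |
|---|---|---|---|
| Constant to year 3, then none | 2.609 | 2.609 | 1.00 |
| Constant to year 3, linear to zero at year 5 | 2.609 | 3.315 | 1.27 |
| Constant to 18 months, linear to zero at year 10 | 2.505 | 4.259 | 1.70 |
| Constant to year 3, linear to zero at year 10 | 2.609 | 4.740 | 1.82 |
| Constant to year 10 | 2.609 | 6.447 | 2.47 |

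With costs held at 3 years, the ratios 1.27 and 1.82 lower cost per QALY by 1 − 1/1.27 = 21% and 1 − 1/1.82 = 45%.

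**Baseline gap.** The article gives no baseline utilities, so a range is assumed. A gap b that is carried forward unadjusted, with no intervention effect, adds b × A(T, 0.10) QALYs per person.

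| Assumed gap | 3 years | 10 years |
|---|---|---|
| 0.01 | 0.025 | 0.061 |
| 0.02 | 0.050 | 0.123 |
| 0.05 | 0.124 | 0.307 |

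**The case against.** **The sentence is garbled, and the mismatch is inferred.** This stands. With a full stop lost after the 10-year period, that period belongs to the QALYs. Read as printed, it can instead qualify the cost-utility ratios, which use both costs and QALYs. On that second reading both run 10 years, and the 60% figure does not apply. The contradiction with the 3-year horizon remains either way. If the wording is an editing slip, correcting it is all that is asked.

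**The horizon is already to be varied.** This is true and relevant, because a 10-year scenario would fit that intention. But no alternative horizon is named, and the 10 years appear in the description of how the result will be calculated, not as a variation on it.

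**The full protocol or analysis plan may settle it.** That would answer an omission. Here the article states two values that cannot both be right.

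**Baseline adjustment may be planned.** This also stands in part. A reader might infer that the QALY comparison is biased towards whichever arm starts healthier. The article does not support that: it nowhere says the QALY difference will be unadjusted. Its Primary endpoint analysis section plans repeated pre-intervention measurements and says: "Due to the lack of randomisation in our sample, other potential confounders at the individual, but also at the setting level, will be also considered". Quality of life is among the primary quantitative outcomes. The Economic analysis section does not carry this over to the QALY formula, so what remains is a risk that one sentence removes.

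**Scope is limited.** Cost per QALY is one of five primary economic outcomes in Table 3. Cost per satisfied patient, cost per responsive patient and the main effectiveness analyses do not use this formula.

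**Conclusion.** The contradiction is established: a 3-year horizon for costs and consequences in one section, and a 10-year period in the section that defines the calculation. It affects a primary economic outcome, and the article describes no basis for extending 18 months of data to 10 years.

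Its size is conditional. A reader might infer that the plan inflates QALY gains 2.5-fold as a matter of course. That figure needs a constant utility difference, QALYs discounted at 10% and costs kept at 3 years, and the article does not show which period is intended. Within those conditions the multiple is 2.47. Across the patterns and rates examined it runs from 1.0 (gain ends by year 3) to 3.33 (constant and undiscounted). The lower end gives the 10-year multiplication no support: a gain that has ended by year 3 should not be multiplied over 10 years.

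**What to change.** Reconcile the two sections, and rewrite the Economic analysis sentence so that its period is unambiguous.

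1. Use one horizon, the 3 years already declared, for both costs and QALYs in the base case.
2. If a 10-year result is wanted, present it as a sensitivity scenario under the existing intention to vary the horizon, with costs over the same 10 years and a stated assumption on how long the utility gain persists. The same statement can cover the part of the 3 years that lies beyond the 18 months observed.
3. State that the QALY difference is adjusted for baseline EQ-5D-5L utility.

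The cost is a few sentences of text. No new measurements are needed, because EQ-5D-5L is already scheduled at the initial survey and at Moments 2 to 5. The data are not all collected: as of December 2025, Project status puts Peru at Moment 3, Nepal at Moment 2 and Mozambique at the start of Moment 2, so the horizon can still be fixed before the final outcomes are known. The downside is a less favourable cost per QALY than a 10-year QALY total set against 3-year costs would show.
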